## Abstract

**Background::**

No studies were located which used a web-based educational intervention to improve the knowledge about newly diagnosed type 2 diabetes mellitus (T2DM). Therefore, the primary objective of the present study was to evaluate the efficacy of web-based educational intervention on psychological outcomes and glycemic control in newly diagnosed T2DM in rural China.

**Methods::**

This work is a part of a comprehensive research project to assess and provide educational intervention that potentially improve psychological status and blood glucose among patients with T2DM. Eligibility criteria for the study includes newly diagnosed with T2DM, adult patients (age ≥30 years) regardless of gender; speak and understand Chinese languages; having no significant comorbidity; being not involved in any trial/study related to diabetes during last 3 months and able to attend regular visits. Eligible participants were divided into 2 groups according to completely randomized design: education group and control group. The outcomes included fasting blood glucose level, EQ-5D-3L questionnaire, Self-rating Anxiety Scale, and Self-rating Depression Scale.

**Results::**

This protocol will provide a reliable theoretical basis for the following research.

**Conclusion::**

The sample came from a single health centre. Therefore, the results can not be generalized for the entire population.

**Trial registration::**

This study protocol was registered in Research Registry (researchregistry6511).

## Introduction

1

Type 2 diabetes mellitus (T2DM) is becoming a threat to people's health all over the world, also in China. The overall prevalence of T2DM in China increased sharply from 0.7% to 9.7% between 1980 and 2010.^[1]^ The dramatic urbanization, the aging population, the rapid change of lifestyle, with increasing overweight and obesity are suggested as possible reasons for the rapid growth of T2DM. The situation regarding T2DM in rural China is even more challenging, with a faster rate of increase of incidence than in the urban areas, while the awareness, treatment, and control of diabetes are less adequate in rural areas.^[2–4]^ Costly hospital care remains dominant in diabetes care in rural areas. Poverty is still a major problem, and affordable and adequate health care is still not available for rural residents.

The primary care services in rural China consists of township health centers and village clinics, and almost all of them are publicly owned. Physicians and nurses in primary care often have low levels of training.^[5,6]^ The most fundamental functions of primary care institutions include implementing basic public health, including establishing health records for residents, health education, and management of chronic diseases. Much of the care of chronic diseases, however, is provided by hospitals and there is little integration between hospitals and primary care services.^[7]^

Nowadays, the internet has become a very popular source of health information for patients in China. Many patients utilize the Internet as a primary resource for information about their disease, and as a means to help them deal with concerns or navigate decisions related to T2DM and improve their knowledge of controlling blood glucose.^[8–10]^ This popularity may relate to advantages, such as immediate access, usually at home, which avoids travel and is cost saving. Patients with T2DM in rural are one such group of users. The present study introduced a web-based education program for patients with T2DM in rural which aimed to support T2DM education and self-management. The program was developed in close cooperation with potential users and is based on national guidelines for diabetes care.^[11]^

Finally, although a number of studies have reported on knowledge evaluation among patients with type 1 and gestational DM, literature related to knowledge evaluation among patients with newly diagnosed T2DM is limited, and no studies were located which used a web-based educational intervention to improve the knowledge about newly diagnosed T2DM. For these reasons, this study focused on evaluating patients of newly diagnosed T2DM in rural China, self-management, healthy diet, exercise, and lifestyle habits.^[12]^

Therefore, the primary objective of the present study was to evaluate the efficacy of web-based educational intervention on psychological outcomes and glycemic control in newly diagnosed T2DM in rural China.

## Materials and methods

2

### Ethical approval

2.1

This work is a part of a comprehensive research project to assess and provide educational intervention that potentially improve psychological status and blood glucose among patients with T2DM. This research project has been registered in the research registry (with number: researchregistry6511) and received ethical approval from the Medical Research and Ethics Committee in Chengyang People's Hospital (no. NMRR-20-903-40294). Also, before the participating in the educational outreach intervention, all health care providers were briefed about the study objectives and the voluntary basis of this participation. After the introductory briefing, the acceptance to take the presession questionnaire implied the participant's consent to participate in the study.

### Study population

2.2

Eligibility criteria for the study includes newly diagnosed with T2DM, adult patients (age ≥30 years) regardless of gender; speak and understand Chinese languages; having no significant comorbidity; being not involved in any trial/study related to diabetes during last 3 months and able to attend regular visits. Participants will be excluded if they are of other types of diabetes (gestational diabetes, T1DM); unable to answer the questionnaire independently or having hearing, vision, or cognitive impairments.

### Random allocation

2.3

Eligible participants were divided into 2 groups according to completely randomized design: education group and control group (Fig. 1). The program duration was 6 months. The education of the patients was accomplished by professional education nurses. All nurses were well-trained.

**Figure 1 F1:**
[figure not shown]
Consolidated Standards of Reporting Trials (CONSORT) diagram of patient flow through the study.

### Intervention and control protocols

2.4

Patients in the intervention group attended the standard clinic-based education and additionally used the web-based education intervention. Access to the web-based education intervention (A touch screen computer) took place at the diabetes clinic at our hospital, supervised by the researcher. The program provided information on healthy diet and healthy lifestyle and included pictures and simple instructions. The program took 15 to 30 minutes to complete. Patients were also given the URL link for the website, so they could access the website as they wished at home.

Patients in the control group attended the standard clinic-based education class alone. The single, group education class, lasting 1.5 hours, is run by Health's dieticians and diabetes educator nurses. Generally 5 to 8 newly diagnosed T2DM patients attend. Session and content is based on healthy diet, exercise, healthy lifestyle, and blood glucose level monitoring.

### Outcomes

2.5

Questions on the patients’ sociodemographic characteristics concerned their age, sex, marital status, level of education, and occupation type (Table 1). Fasting blood glucose level was measured in mmol/L from a venous blood sample. Health-related quality of life was measured by the EQ-5D-3L questionnaire, which is a validated generic instrument used in clinical settings for general population and for economic evaluation. Based on the real-time information, we would also assess the patient conditions and offer corresponding suggestions for better self-management. The Self-rating Anxiety Scale and Self-rating Depression Scale are the scales for assessing anxiety and depression, which includes 20 problems respectively, using a 4-point scale ranging from 1 (none, or a little of the time) to 4 (most, or all of the time). The statistical score of all questions were calculated after completion of the answers (Table 2).

**Table 1 T1:** Patient baseline demographics.

Demographics	Education group	Control group	*P* value
Number of patients			
Age^†^ (years)			
Male sex (no. [%])			
BMI^†^ (kg/m^2^)			
Follow-up^†^			

BMI = body mass index.

† The values are given as the mean and the SD.

**Table 2 T2:** Postoperative outcomes.

Outcomes	Education group	Control group	*P* value
Fasting blood glucose level^†^			
EQ-5D-3L questionnaire^†^			
Self-rating Anxiety Scale^†^			
Self-rating Depression Scale^†^			

† The values are given as the mean and the SD.

### Statistical analysis and power analysis

2.6

The analyses will be performed using SPSS 22.0.0 (SPSS Inc., Chicago, IL). Frequencies and descriptive statistics will be used for patients’ demographic presentation, while means and standard deviations will be calculated for the continuous variables and group differences will be analyzed by using Pearson chi-square test for categorical variables. Kolmogorov–Smirnov test will be applied to check the distribution of data. Independent t test will be used in case of normally distributed data, whereas, Mann–Whitney *U* test for non-normal distributions. *P* <0.05 will be considered as significant for all analysis.

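### A normality pre-test chooses between the t test and Mann–Whitney U, but Table 2 shows mean and SD throughout, so the P value may not test the difference displayed.

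*Protocol article*

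**What the plan says.** Section 2.6 (Statistical analysis and power analysis) sets a two-step rule. A Kolmogorov–Smirnov "test will be applied to check the distribution of data". Then "Independent t test will be used in case of normally distributed data", and otherwise the Mann–Whitney U "test for non-normal distributions". The threshold is P "<0.05 will be considered as significant for all analysis".

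The same section says that "means and standard deviations will be calculated for the continuous variables" and names no other summary for data that fail the pre-test. In section 2.5, every row of the Table 2 shell (fasting blood glucose, EQ-5D-3L, Self-rating Anxiety Scale, Self-rating Depression Scale) carries the footnote "The values are given as the mean and the SD". The shell has one column per group and one for the P value.

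**The concern.** The t test compares means. Mann–Whitney U compares ranks: it responds to the probability that a patient in one arm scores higher than a patient in the other. The two agree when one arm is a shifted copy of the other, but not in general when the arms differ in shape.

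The article fixes both the rule and the table, and they fit together on only one branch. On the other branch, a reader of Table 2 sees two means and two SDs beside a P value that answers a different question, and the table holds no figure for what was tested. Equal means can stand beside a significant P value, or clearly different means beside a non-significant one. All four outcomes are exposed, so both halves of the primary objective (psychological outcomes and glycemic control) are affected.

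**Working it through.** **Inputs.** From the article: the selection rule, mean and SD for all outcomes, and the 0.05 threshold (taken as two-sided, since the article does not say). The article reports no sample size, SD, effect size or power, so there is no figure to reproduce. Every distribution and sample size below is an assumption chosen to show how the rule behaves.

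**1. Equal means, different shapes.** Assume a bounded score.
- Education arm: 70% of patients at 1.0 and 30% at 0.60.
- Control arm: 40% at 1.0 and 60% at 0.80.

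Means: 0.7 × 1.0 + 0.3 × 0.60 = 0.88, and 0.4 × 1.0 + 0.6 × 0.80 = 0.88.

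SDs (gap between the two values × √(p(1−p))): 0.40 × √(0.7 × 0.3) = 0.18, and 0.20 × √(0.4 × 0.6) = 0.10.

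Rank comparison:
- P(E>C) = 0.7 × 0.6 = 0.42
- P(tie) = 0.7 × 0.4 = 0.28
- P(E>C) + ½P(tie) = 0.42 + 0.14 = 0.56, against 0.50 if neither arm tended to score higher

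The expected table entries are 0.88 (0.18) and 0.88 (0.10). In 4,000 simulated trials with 100 per arm, Mann–Whitney gave P<0.05 in 38% to 39% and Welch's t test in about 5%. The Kolmogorov–Smirnov test, even uncorrected, rejected normality in the education arm in every trial. Applied by arm, the plan's rule would therefore select Mann–Whitney here.

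**2. The whole rule on a continuous outcome.** Assume a mean of 8 in both arms, control normal with SD 1.5 and education right-skewed (4 plus a lognormal with mean 4 and log-SD 0.5). The pre-test is the Lilliefors form, and failure in either arm selects Mann–Whitney (3,000 trials per row).

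| Per arm | Mann–Whitney selected | Selected and P<0.05 | t test P<0.05 | Selected, P<0.05, means in the opposite direction |
|---|---|---|---|---|
| 50 | 73% | 10.9% | 5.4% | 0.2% |
| 100 | 94% | 21.8% | 4.7% | 0.1% |
| 200 | >99% | 38.0% | 4.6% | 1.7% |

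**3. Reversal is possible.** A data set constructed with 50 per arm has education mean 9.0 (SD 4.7, median 6.9) and control mean 8.0 (SD 0.9, median 8.0). Normality is rejected in the education arm. Mann–Whitney gives P=0.0004, favouring lower values with education, while the displayed education mean is 1.0 higher. The t test gives P=0.14.

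**4. Which branch is taken.** For one mildly skewed variable (lognormal, log-SD 0.35), the proportion of samples failing the pre-test, as ranges over repeated simulation runs, is:

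| n | Uncorrected K–S | Lilliefors-corrected K–S |
|---|---|---|
| 50 | 2% to 3% | 44% to 45% |
| 200 | 39% to 44% | 95% to 97% |

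The variable is the same in every cell. Only the sample size and the form of the test change.

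**5. Type I error.** When both arms were drawn from one distribution (a lognormal or a score with half of patients at the ceiling; 30 to 100 per arm where recorded), the two-step rule rejected in 4.4% to 5.8% of trials across the runs.

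**The case against.** Several points on the other side stand.

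- **The rule is written down in advance.** A reader might infer that the analysis is left open until the data are seen. That goes too far: the article states which test follows from which result. The rule is data-dependent but not open-ended. The variant of the pre-test and whether it is run by arm may be settled in a fuller document, and their absence here is no finding.
- **There is no general inflation of error.** A reader might infer an excess of false positives. Step 5 does not show one when the arms share a distribution.
- **The discordance needs arms of different shape.** Nothing in the article suggests that education would produce the shapes in steps 1 to 3. Under a simple 15% proportional lowering of glucose (also an assumption), none of 3,000 trials at 50 or at 100 per arm gave a significant Mann–Whitney P value with the means reversed.
- **EQ-5D-3L cannot be singled out.** It is tempting to say that this score will fail the pre-test. The article does not say how it will be scored or how it is distributed, so the example in step 1 is not a statement about it.
- **An empty shell does not prove that no interval will be reported.** The absence of a confidence interval column is not itself held against the plan.

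None of this removes the mismatch. The article states both the test rule and the mean-and-SD presentation, so this is two stated elements that do not fit, not detail left to another document.

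**Conclusion.** The point holds as a mismatch between what is tested and what is shown. On the Mann–Whitney branch, the P value in Table 2 does not test the difference in the means beside it, and the branch can turn on sample size and on the form of the pre-test.

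The more likely harm is a significant P value beside near-equal means, or the converse. In the assumed equal-mean scenarios, the rank test was significant in about 11% to 38% of trials, against about 5% for a test of means. These figures rest wholly on assumed distributions and sample sizes. They show what the rule can do, not what this trial will produce. Reversal of direction was at most 1.7% in the scenario simulated. The documents do not support a claim of general type I error inflation or of an analysis left unspecified. The defect is worth correcting because it reaches every outcome and the correction is cheap.

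**What to change.** In section 2.6, delete the Kolmogorov–Smirnov selection step. Name Welch's t test, reported as a difference in means with its 95% CI, as the analysis of all four outcomes. Keep Mann–Whitney U as a named sensitivity analysis. Add a column to Table 2 for the mean difference (95% CI), so that the P value, the means and the estimate refer to one quantity. Adjust for the baseline value of an outcome only if that value is collected; the article does not clearly show that it is, and the Table 1 shell lists none of the four.

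The cost is a few lines of analysis text and one table column, with no change to data collection. The downside is possibly slightly lower power than a rank test for a heavily skewed outcome.

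### The arms are compared with unadjusted two-sample tests and no baseline outcome value, which gives up precision and leaves chance imbalance uncorrected

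*Protocol article*

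**What the plan says.** Section 2.6 names the between-arm methods for continuous variables. A Kolmogorov–Smirnov "test will be applied to check the distribution of data". After that, "Independent t test will be used in case of normally distributed data", and the Mann–Whitney U "test for non-normal distributions". P below 0.05 "will be considered as significant for all analysis". The section mentions no covariate, change score, regression or ANCOVA.

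The four outcomes (fasting blood glucose, EQ-5D-3L, Self-rating Anxiety Scale, Self-rating Depression Scale) appear only in Table 2, titled "Postoperative outcomes". It has one column per arm and a P value, and its footnote reads "The values are given as the mean and the SD". Table 1, "Patient baseline demographics", lists number of patients, age, sex, BMI and follow-up, and none of the four outcomes.

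Section 2.3 describes complete randomisation into two groups and states no stratification. It gives six months as the length of the program, but no section states when the outcomes are assessed.

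**The concern.** The stated objective is the effect on psychological outcomes and glycaemic control, so these four comparisons are the trial's result. A two-sample test on post-intervention values treats all variation between patients as noise, including the part that a pre-randomisation measurement of the same quantity would predict. Two things are at stake. The confidence interval is wider, and the power lower, than the same patients could give. Also, nothing in the described allocation restrains a chance difference in baseline glucose or anxiety, and part of any such difference stays in the estimate. With no baseline outcome in Table 1, a reader could not see that it was there.

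This is not a detail left to an unseen analysis plan. The article names the tests and lays out the results table.

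**Working it through.** The article states no sample size, SD, effect size or power, although Section 2.6 has power analysis in its heading. There is therefore no figure to reproduce, and the numbers below are illustrations.

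**Assumptions, none from the article:** r = 0.3, 0.5 or 0.7; 1:1 allocation; two-sided alpha 0.05; standardised difference 0.5; 50 patients per arm for the power and imbalance examples.

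**1. Variance.** Relative to the unadjusted comparison of follow-up values, ANCOVA has variance 1 − r² and a change score has 2(1 − r).

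| r | ANCOVA | Change score | Equivalent gain in sample, 1/(1 − r²) |
|---|---|---|---|
| 0.3 | 0.91 | 1.40 | 1.10 |
| 0.5 | 0.75 | 1.00 | 1.33 |
| 0.7 | 0.51 | 0.60 | 1.96 |

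**2. Power, 50 per arm.** The standard error of the unadjusted difference is √(2/50) = 0.2 SD. Power is about Φ(0.5/(0.2√(1 − r²)) − 1.96).
- Unadjusted: Φ(2.50 − 1.96) = 70.5%
- ANCOVA, r = 0.5: Φ(2.887 − 1.96) = 82.3%
- ANCOVA, r = 0.7: Φ(3.501 − 1.96) = 93.8%

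**3. Sample size for 80% power.** Unadjusted, 2(1.96 + 0.8416)²/0.5² = 62.8, so 63 per arm. Multiplying 62.8 by 0.91, 0.75 and 0.51 and rounding up gives 58, 48 and 33 per arm.

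**4. Carry-over of imbalance.** Given a baseline difference b, the unadjusted estimate shifts by r × b. With 50 per arm, b has SD 0.2.
- b = 0.2 (one standard error): shift 0.06, 0.10, 0.14 SD for r = 0.3, 0.5, 0.7
- b = 1.96 × 0.2 = 0.392: shift 0.12, 0.20, 0.27 SD

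**5. Type I error given the imbalance.** Write b as k standard errors. The probability of rejecting a true null is 1 − Φ((1.96 − rk)/√(1 − r²)) + Φ((−1.96 − rk)/√(1 − r²)), in which n cancels.
- k = 1.96: 7.9%, 12.9%, 20.5% for r = 0.3, 0.5, 0.7
- k = 1: 5.0%, 4.8%, 3.9%

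Averaged over all randomisations, the rate is 5%. The inflation belongs to the less common, larger imbalances.

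**The case against.** The strongest reply is that the planned test is sound and the documents settle less than they seem to. Four readings are tempting and go too far.

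- *That the plan expressly restricts the test to follow-up values.* No sentence says so. It is inferred from the Table 2 shell, and the shells are imperfect: Section 2.5 refers to marital status, education and occupation as in Table 1, which does not list them, and the title of Table 2 refers to surgery in a trial that has none. A t test on change scores is not excluded. This would not rescue the plan, since a change score has a higher variance than ANCOVA at each r shown.
- *That baseline scale scores are collected and then discarded.* Section 2.1 says "the acceptance to take the presession questionnaire implied" consent, but this follows a sentence about briefing health care providers. Nothing describes the questionnaire or links it to the scales.
- *That the test is biased or its error rate wrong.* Over randomisations it is unbiased and keeps its 5% level.
- *That a baseline difference enters the result in full.* Only the fraction r does.

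The size of the gain is also open to doubt. The Discussion calls medication adjustments inevitable and does not take them into account, so r for fasting glucose may be low. At r = 0.3 the gain is worth only 1.10 times the sample. All of this stands as a limit on the point. What remains is that the tests named take no covariate and no baseline outcome appears anywhere in the tables or analysis.

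**Conclusion.** The point holds as a matter of efficiency and of protection against chance imbalance, not of validity. The unadjusted comparison is a stated choice, and a better one is standard. Adjustment would cut the variance by 9%, 25% or 49% at r of 0.3, 0.5 or 0.7. An unusually large imbalance (1.96 standard errors) would raise the conditional type I error of the planned test to between 7.9% and 20.5%.

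The variance figures depend on r alone, and the power and shift figures also on an assumed sample size; the article gives neither r nor n. The benefit can be had only for outcomes whose baseline value exists or can still be collected. The change should be made, but the planned analysis would not be wrong without it.

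**What to change.** In Section 2.6, make the primary comparison of each outcome an ANCOVA of the post-intervention value on arm, with that outcome's baseline value as covariate. State when the post-intervention value is taken. In Table 2, report the adjusted mean difference with its 95% CI.

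For non-normal data, judge the residuals. If they are clearly non-normal, use robust or bootstrap standard errors, or add a rank-based ANCOVA as a sensitivity analysis.

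State in Section 2.5 that fasting glucose, EQ-5D-3L and both self-rating scales are recorded before allocation, and add these values to Table 1. Parts of the methods are written in the past tense. If enrolment is already complete, adjust those outcomes that have a baseline value, and say which do not.

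Cost: revised wording, two table shells and slightly more analysis work. If baseline values are not already collected, add three short questionnaires and one routine glucose value at the entry visit.

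### Four unranked outcomes are each called significant at P<0.05 with no success rule: if any one may count, the chance of at least one two-sided false positive is up to 18.5%

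*Protocol article*

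**What the plan says.** The Introduction states that "the primary objective of the present study was to evaluate the efficacy of web-based educational intervention on psychological outcomes and glycemic control", and the Abstract and the Discussion repeat this. It is one objective over two domains.

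The Abstract (Methods) gives the outcomes: "The outcomes included fasting blood glucose level, EQ-5D-3L questionnaire, Self-rating Anxiety Scale, and Self-rating Depression Scale". Section 2.5 describes the same four, and Table 2 gives each its own P-value cell. None is called primary or secondary. Section 2.5 introduces one of them in different terms from the objective: "Health-related quality of life was measured by the EQ-5D-3L questionnaire".

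Section 2.3 has two arms, so there is one comparison per outcome. Section 2.6 assigns the test ("Independent t test will be used in case of normally distributed data", otherwise Mann-Whitney) and sets the threshold: P below 0.05 "will be considered as significant for all analysis".

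**The concern.** A single threshold for every analysis works when one outcome carries the primary claim. Here the claim rests on up to four outcomes of equal standing, and the text does not say whether success needs both domains, either domain, or any one outcome. A better anxiety score with unchanged glucose could be called a success or a failure after the data are seen. Under the most permissive reading, the error rate of the primary objective is well above the 5% that the stated threshold suggests.

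**Working it through.** **Figure to reproduce.** The article gives no family-wise error rate, so the only stated figure is the per-test level of 0.05 (section 2.6).

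**Inputs from the article.** Four outcomes (Abstract, section 2.5 and Table 2); two arms (section 2.3); 0.05 per test (section 2.6).

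**Assumptions, because the article does not give them.** Tests are two-sided. The correlations between outcomes are as stated below. Any one significant outcome may be read as meeting the objective. There is no true effect on any outcome.

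**1. Four independent outcomes.** 1 - (1 - 0.05)^4 = 1 - 0.8145 = 0.185, or 18.5%. The Bonferroni upper bound is 4 x 0.05 = 20%.

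**2. Correlated outcomes** (simulated four-variate normal statistics, each tested at |z| > 1.96):

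| Assumed correlation | At least one two-sided false positive |
|---|---|
| Questionnaires 0.3, glucose independent | about 18% |
| Questionnaires 0.5, glucose independent | about 17% |
| Questionnaires 0.7, glucose independent | about 15% |
| All four pairwise 0.7 | 13.0% |
| All four pairwise 0.8 | 11.4% |
| All four pairwise 0.9 | 9.4% |

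**3. EQ-5D-3L outside the family.** Three independent outcomes: 1 - 0.95^3 = 0.143, or 14.3%. With assumed correlations, about 12.3-13.6%.

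**4. False results favouring education only.** Each two-sided test at 0.05 has probability 0.025 in that direction.
- One outcome: 2.5%.
- Four independent outcomes: 1 - 0.975^4 = 0.096, or 9.6%.
- Four outcomes with glucose correlated 0-0.2 with the questionnaires, and the questionnaires more strongly with one another: about 7.7-9.0%.

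**5. The same four outcomes under adjustment.** At 0.05/4 = 0.0125 each, independent outcomes give 1 - (1 - 0.0125)^4 = 0.049, or 4.9%. This is also Holm's error rate when no outcome has a true effect, because its first step compares the smallest P with 0.0125.

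**The case against.** A reader might infer that the trial has a 15-18.5% chance of a false claim of efficacy. The documents do not support that, for four reasons.

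- **Direction.** The 15-18.5% counts significant results in either direction, including those favouring control, which nobody would report as efficacy. The figure for results favouring education is about half.
- **Correlation.** The article gives none. The 15% end needs moderate correlation among the questionnaires and little with glucose. Strong correlation among all four takes it to 9-13%.
- **Decision rule.** Section 2.6 defines significance for a test, not success for the trial. The objective joins its two domains with a conjunction. If both were required, with independent tests and no true effect anywhere, the chance in either direction would be 0.05 x 0.0975 = 0.5% with the two psychological scales, or 0.05 x 0.143 = 0.7% with EQ-5D-3L added. It would be higher if one domain truly responds. With a real glucose effect that is almost certain to be detected, it approaches 9.75% for two independent scales (1 - 0.95^2).
- **Family.** EQ-5D-3L is described as quality of life, and the objective does not name that domain.

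All four stand, and they limit what the number may be called.

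It can also be said that a condensed article may leave multiplicity to an analysis plan that is not shown. That carries less weight here. The article is not silent: it fixes one threshold for every analysis, and a plan that applied a stricter one to any of these outcomes would contradict it. The threshold, the unranked list and the two-domain objective are all stated in the text.

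**Conclusion.** The point holds as a conditional statement. The article fixes 0.05 for every analysis, ranks none of four outcomes and does not define success for a two-domain objective, so the error rate of that objective is not controlled.

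If any one significant outcome may count, the rate for at least one two-sided false positive is 18.5% at independence. It falls to the lower values above under the assumed correlations or with the smaller family. Measured as a false result favouring education, it is about 8-10% where a single outcome would give 2.5%, so three to four times as large.

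No single figure can be presented as the trial's error rate, because the success rule, the family and the correlations are not stated. The defect itself depends on none of those figures: the rule that would determine the rate is absent, while the threshold that drives it is fixed.

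**What to change.** **Main option.** In section 2.6, replace the blanket threshold for the efficacy outcomes by wording such as: *The between-group comparisons of the outcomes that form the primary objective are tested with Holm's procedure at an overall two-sided level of 0.05; an effect is claimed only for outcomes that remain significant after adjustment.* List those outcomes: all four, or three if EQ-5D-3L is declared secondary.

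**Alternative.** The sponsor names one primary outcome and its assessment time before outcome data are seen by group, and tests it at two-sided 0.05. The others are tested with Holm only if the primary is significant, or are reported as supportive. The gate matters: a primary at 0.05 alongside an ungated Holm family at 0.05 leaves overall error at up to about 1 - 0.95 x 0.95 = 9.75% under independence. The choice of outcome belongs to the sponsor. The time point has to be stated too, since the 6 months in section 2.3 is the programme duration and not a stated assessment time.

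**Cost.** Under Holm, the smallest P is compared with 0.0125 (0.05/4) among four outcomes or 0.0167 (0.05/3) among three, with slightly lower power per outcome. The article gives no sample size or effect size from which to quantify that loss. The alternative keeps 0.05 for one outcome, but the objective in the Abstract, Introduction and Discussion must then be reworded to match. Either way the change is to text, and no further data are needed.
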